### Data analysis

The primary method of analysis will be provision of descriptive statistics characterizing key app features, such as viewing of money saved, viewing of quit days, achievement sharing, and crave logging. We will examine descriptive and qualitative data in the context of the fit between individuals, task and technology (FITT) framework [24]. The FITT framework is prevalent among human-computer interaction studies and often used in mobile health research [25]. It posits a strong relationship between individual, task, and technology, and was adopted to assess feasibility and usability in a holistic manner. The FITT approach will help to assess how usability and feasibility metrics are interrelated, and the cyclic effects with relation to the user. We will identify associations between survey Likert-scale responses (i.e., usability and feasibility measures) and quantitatively measured actions from app log data. Given the ordinal data and unknown distributions, the Mann-Whitney U test will be used for statistical analyses.

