### Outcomes

As this study seeks to assess feasibility, the primary data will include (1) recruitment rates, (2) retention rates, and (3) adherence, measured through user engagement with the app. High usability measures correlate strongly with effective interventions [20]. Engagement with the app will be measured using both survey data in conjunction with logged data from the app itself. Logged data will include specific features that are used as well as patterns of activity (e.g., checking the current money saved after viewing a motivational message). We are particularly interested in the use patterns of two popular features in many cessation apps: calculator and calendar. Measures of usability are based on principles from ubiquitous computing guidelines [21]. These concepts will include (1) attention (e.g., “How many times did you use Kwit per day?”); (2) trust (e.g., “Were you able to complete tasks with ease?”); (3) conceptual model (e.g., “Did Kwit behave as expected?”); (4) interaction (e.g., “Was Kwit frustrating to use?”); and (5) impact (e.g., “How comfortable were you using Kwit in social settings?”). Following guidelines for evaluating the usability of medical applications [22], responses will be either yes/no, or chosen from a Likert scale of 1–9 (a longer Likert-type scale was selected to minimize the risk of a ceiling effect). These questions will be paired with open-ended qualitative questions and comments that will complement numerical ratings. For example, an interaction question will first ask the user: “Was Kwit frustrating to use?” with a 1–9 Likert scale option, followed by the open-ended question: “Please describe an example of how Kwit was frustrating to use.”

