### Power calculations

In a feasibility pilot trial, it is inappropriate to consider mean outcomes due to the lack of power [17, 18]. However, we will still calculate standard deviation of the differences between the intervention and control groups at 1 month, which is a standard time for tobacco cessation treatment. These data can help inform the calculations needed for a larger RCT.

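### A significance test is the only tool named for identifying rating-by-log associations in about 20 app users; these should be exploratory estimates with intervals, not a way to select features

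*Protocol article*

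**What the plan says.** In the protocol article, the Data analysis section opens with description: "The primary method of analysis will be provision of descriptive statistics characterizing key app features", with examples "such as viewing of money saved, viewing of quit days, achievement sharing, and crave logging". It then adds a second step: "We will identify associations between survey Likert-scale responses (i.e., usability and feasibility measures) and quantitatively measured actions from app log data". The tool for that step follows at once: "Given the ordinal data and unknown distributions, the Mann-Whitney U test will be used for statistical analyses". No other inferential method is named there, and no significance level or number of comparisons is given.

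The Outcomes section lists five usability concepts (attention, trust, conceptual model, interaction, impact) and says that "responses will be either yes/no, or chosen from a Likert scale of 1–9". It also singles out two features: "We are particularly interested in the use patterns of two popular features in many cessation apps: calculator and calendar".

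The Recruitment section plans 10 men and 10 women per group, so 20 app users. The Sample size section takes 20 from usability-testing recommendations, doubles it for stratification by sex, and allows further recruitment if needed. The Power calculations section states: "In a feasibility pilot trial, it is inappropriate to consider mean outcomes due to the lack of power".

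The Intervention section says that the study's data will help pick out the app components with the most promise. The Discussion sees the data feeding larger trials.

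**The concern.** Logged actions exist only for people who have the app, so each rating-by-log association is examined within one arm of about 20. The protocol declines to consider mean outcomes in a 20 v 20 comparison because power is lacking, yet it assigns a hypothesis test to associations in half that number.

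If the test decides which associations count as identified, two things follow. Across several pairs, some may pass by chance. A real association of moderate size will usually fail, and when it passes its size will be exaggerated. Because the Intervention section intends to learn which components look promising, such a filter could carry the wrong features, or inflated effects, into the planning of the next trial.

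**Working it through.** **The plan's own figure.** 20 from the usability recommendation × 2 sexes = 40. Allocation 1:1 gives 40/2 = 20 app users, 10 of each sex. This reproduces. The protocol gives no alpha, power or effect size, so there is no power figure to reproduce.

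**Assumptions that are not in the protocol.** Two-sided alpha of 0.05; one rating per concept; each feature's log data split into two groups, because a Mann-Whitney test needs two groups and none is defined; a normal shift for the power calculation.

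**1. Chance results.** Crossing five concepts with the four example features gives 5 × 4 = 20 pairs. With no true association:
- Expected false positives: 20 × 0.05 = 1.0.
- Chance of at least one, if independent: 1 − 0.95^20 = 0.64.
- For other numbers of independent tests, by the same formula: 5 tests 0.23, 10 tests 0.40, 30 tests 0.79.

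The pairs share users and will be correlated. Mann-Whitney tests were therefore simulated in 20 users, with 1–9 ratings and features split at the median (1,000 runs per row). The correlation is that among ratings and, separately, among features:

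| Correlation | At least one false positive | Mean number |
|---|---|---|
| 0 | 61% | 0.90 |
| 0.3 | 59% | 0.93 |
| 0.5 | 54% | 0.97 |
| 0.7 | 40% | 0.92 |

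Correlation lowers the chance of any false positive but leaves the expected number at about 0.9. With 14 users the chance ranges from 35% to 54%.

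**2. Power and exaggeration for one test.** Exact Mann-Whitney, 4,000 simulated samples per row:

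| Split | True difference | Power | Mean estimate when p < 0.05 |
|---|---|---|---|
| 10 v 10 | 0.5 SD | 16% | 1.09 SD |
| 10 v 10 | 0.8 SD | 36% | 1.23 SD |
| 10 v 10 | 1.0 SD | 52% | 1.30 SD |
| 7 v 7 | 0.5 SD | 12% | 1.27 SD |
| 7 v 7 | 0.8 SD | 23% | 1.43 SD |

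At 10 v 10, inflation is 1.09/0.5 = 2.2-fold for a true 0.5 SD and 1.23/0.8 = 1.5-fold for a true 0.8 SD. The difference needed for 80% power is (1.96 + 0.84) × √(2/(10 × 0.955)) ≈ 1.28 SD, where 0.955 is the efficiency of the Mann-Whitney test under normality.

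The second set of results does not depend on how many pairs are examined.

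**The case against.** Much can be said for the plan. Descriptive statistics are primary, the results are to be read alongside qualitative data, and the leading outcomes (recruitment, retention, adherence) do not hang on this test. Exploratory tests in a pilot are not in themselves an error. All of this stands, and it limits how far the point can go.

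Several stronger readings are tempting but unsupported:

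- *That at least 20 tests will be run.* Twenty is a product of five concepts and four features offered only as examples. The number of items per concept is not given, and some responses are yes/no while the planned associations concern Likert ratings. The true count could be lower or higher.
- *That at most 20 users will contribute.* Twenty is the planned arm size. The Sample size section permits more recruitment, and dropout would reduce the number.
- *That the protocol itself calls this analysis underpowered.* Its remark concerns mean outcomes. Extending it to associations within one arm is a fair inference, not the protocol's statement.
- *That chance associations will be reported as established.* No significance threshold, selection rule or confirmatory claim is stated. The risk is real but the outcome is not fixed.
- *That a multiplicity rule is missing.* One may sit in an analysis plan that is not shown, so its absence is no finding.
- *That heavy dropout would multiply false positives.* The 33% retention quoted in the Background refers to traditional programmes. If it applied here, about 7 users would remain; split 4 v 3, the smallest two-sided exact p-value is 2/35 = 0.057, so no result could reach 5%.

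What survives is the choice that the article does fix: a significance test is the only tool named to identify these associations, and the data have a declared use in picking out components.

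**Conclusion.** The point holds in a limited form. Choosing or highlighting features by test result would be unreliable in this arm: a moderate true difference is missed about two times in three (0.8 SD) to five times in six (0.5 SD) at 10 v 10, and a significant estimate of a true 0.5 SD averages about twice the truth. If 20 pairs were tested at 5% with nothing there, about one would be expected to pass, with a 40% to 64% chance of at least one; for five independent tests the chance is 23%. These figures rest on the assumed alpha, the assumed number of pairs, an even split and a normal shift.

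The case for change rests mainly on low power and exaggeration, which hold whatever the count of pairs. The main feasibility outcomes are unaffected.

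**What to change.** In the Data analysis section, state that the rating-by-log associations are exploratory. Report every pair examined as an effect size with a 95% confidence interval, in one complete table, and say that statistical significance will not be used to select features. This brings the end of the section into line with its descriptive opening. Banning p-values altogether is not necessary, and a focus on calculator and calendar is already in the Outcomes section.

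The intervals will be wide: for a 10 v 10 split, roughly ±1.96 × √(2/10) = ±0.88 SD. That is an honest picture of what about 20 users can show.

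The cost is wording only, with no change to recruitment or data collection. The small downside is that no significant association can be claimed.

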### Power calculations

In a feasibility pilot trial, it is inappropriate to consider mean outcomes due to the lack of power [17, 18]. However, we will still calculate standard deviation of the differences between the intervention and control groups at 1 month, which is a standard time for tobacco cessation treatment. These data can help inform the calculations needed for a larger RCT.

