### Recruitment

Over a 6-month period, we will recruit 40 young adult smokers aged 18–30 years who are interested in smoking cessation. Participants will receive a TTS counseling session focused on motivational interviewing and then be randomized 1:1 to either standard patient-initiated follow up (through the state Quitline) or use of the Kwit app for 1 month. Participants will be stratified by sex at a 1:1 ratio (10 male and 10 female participants in each group) because men and women are known to have highly variable responses to existing tobacco control interventions [16]. The recruitment procedure will follow existing processes currently being implemented by the TTS. In FY2016, there were 3078 everyday smokers that consented to receive TTS counseling and additional follow up. Of that population, 363 (11.8%) were aged 18–30 years. Therefore, a 6-month recruiting period would expect to identify approximately 181 potential young adult smokers to meet the eligibility criteria. Stratification by sex as planned is highly feasible because roughly half of all TTS-identified individuals were male. While the recruitment of 40 individuals from about 181 who are eligible (22%) seems highly feasible to the TTS team, we have developed contingency plans for recruitment should numbers fall short. Individuals will be compensated for their time to participate in follow-up interviews at the end of 1 month.

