### Sample size

Given this is a feasibility trial, a formal sample size calculation is not appropriate [17]. For the current study, we are informed by quantitative usability-testing recommendations that suggest a sample size of 20 [19]. Because we wish to stratify by birth sex, we obtained our sample size of 40 individuals. While we expect this to be more than sufficient, we will remain flexible in our approach and will recruit additional individuals if necessary.

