### Randomization

Participants who are eligible will be randomized to either a smartphone experimental group or patient-initiated follow up (usual care) by the research team. They will be stratified by gender, and will be randomized in total using a 1:1 ratio. Neither the participant nor the research team will be blind to their status. An independent statistician will generate an allocation table using Stata’s *ralloc* function. That list will be provided to a member of the research recruitment team, who will upload the table into the Research Electronic Data Capture (REDCap) online survey. Neither the principal investigator (PI) nor any researcher conducting analyses will have access to the randomization process or allocation table. Once recruitment has started, participants that have consented to the study will then be assigned by REDCap to either the experimental or control arms based on the allocation order.

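### Sex sets the stratification and doubles the sample to 40, but the stated analyses and the planning SD make no use of it

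*Protocol article*

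**What the plan says.** Three sections of the protocol article build sex into the design.

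- **Recruitment** plans 10 men and 10 women per arm, "because men and women are known to have highly variable responses to existing tobacco control interventions".
- **Sample size** starts from "quantitative usability-testing recommendations that suggest a sample size of 20" and continues: "Because we wish to stratify by birth sex, we obtained our sample size of 40 individuals". No other reason for the doubling is given.
- **Randomization** confirms it: "They will be stratified by gender, and will be randomized in total using a 1:1 ratio".

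Two sections describe what is done with the data, and neither mentions sex.

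- **Data analysis** makes descriptive statistics of app features the primary method, then describes associations between survey ratings and app log data, and ends by saying that "the Mann-Whitney U test will be used for statistical analyses".
- **Power calculations** promises the "standard deviation of the differences between the intervention and control groups at 1 month" as an input to the design of a larger randomized trial.

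**The concern.** Randomization can be stratified at any sample size. Doubling the sample on account of sex makes most sense if something is then estimated by sex or adjusted for it, and the article describes no such step. It does name its primary method, its test and its planning quantity, so the analysis is not left wholly to another document.

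What is at stake is the usefulness of the pilot's output. Under Study objectives, the secondary aim is to supply information for a fully powered trial. If the SD mixes men and women and no split by sex is shown, the designers of that trial cannot tell whether stratifying or adjusting for sex is worthwhile. If they do adjust, their variance input will be somewhat too large.

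**Working it through.** **1. The plan's own figure.** 20 × 2 sexes = 40, and 40 / 2 arms / 2 sexes = 10 per cell. Both match the article. It states no alpha, power or effect size, so there is nothing further to reproduce.

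**2. Effect of leaving sex out of the SD.** I read the planning quantity as the within-arm SD of a 1-month outcome, pooled over arms. Let σ be the SD within arm and sex, and d the difference between the sexes in units of σ. With equal numbers of men and women in each arm:

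variance ignoring sex = σ² × (1 + d²/4), so the SD ratio is sqrt(1 + d²/4).

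A future sample size for a comparison of means scales with the variance. The article gives no d, so these values are assumptions. The last column is illustrative: a target effect of 0.5σ, two-sided 5%, 80% power, against 63 per arm with the within-sex SD.

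| Assumed d | SD ratio | Variance (future N) ratio | Future n per arm |
|---|---|---|---|
| 0.2 | 1.005 | 1.01 | 64 |
| 0.5 | 1.031 | 1.0625 | 67 |
| 0.8 | 1.077 | 1.16 | 73 |
| 1.0 | 1.118 | 1.25 | 79 |

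**3. Sex differences that vary by arm.** The stated rationale concerns response to intervention, so d may differ between arms. With d₁ and d₂ in the two arms, the pooled factor is sqrt(1 + (d₁² + d₂²)/8). If the sexes differ only in the app arm, by 1σ, it is sqrt(1.125) = 1.061, or about 6%.

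**4. Binary outcome.** Assume cessation of 30% in one sex and 10% in the other. Ignoring sex, the variance is 0.20 × 0.80 = 0.16. Within sex it is (0.30 × 0.70 + 0.10 × 0.90)/2 = 0.15. The SD ratio is sqrt(0.16/0.15) = 1.033. For 40% and 10%, the variances are 0.1875 and 0.165, and the SD ratio is 1.066.

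**5. Against sampling error.** The 95% chi-square interval for an SD runs from sqrt(df/χ²₀.₉₇₅) to sqrt(df/χ²₀.₀₂₅) times the estimate, assuming a roughly normal outcome and complete follow-up.

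- 40 people, 38 df (arm means removed): 0.82 to 1.29.
- 40 people, 36 df (arm-by-sex means removed): 0.81 to 1.30.

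Even at d = 1, the within-sex SD is 1/1.118 = 0.89 of the unadjusted SD, which lies inside the lower limit of 0.82. Taking the SD within sex costs two degrees of freedom and almost no precision.

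**6. Precision of results by sex.** With 10 per sex per arm and an assumed 20% cessation rate, the 95% half-width of a sex-specific risk difference is 1.96 × sqrt(2 × 0.2 × 0.8/10) = 0.35. An SD from 10 people has an interval of 0.69 to 1.83 times the estimate. Such results can only be descriptive.

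**The case against.** The strongest reply is that the article is silent and not wrong. It does not say that the SD is pooled over sex, and a condensed article may leave the handling of strata and tables by sex to the full protocol or analysis plan. This stands against one inference that a reader might draw, namely that no result by sex will be produced. The text supports only that the stated analyses make no use of sex.

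A reader might also conclude that the stratification is wasted. It is not: it balances sex across arms and secures 10 men and 10 women in each, whatever the analysis.

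A third tempting reading is that the Mann-Whitney test is misapplied, because an unstratified rank test after stratified allocation is conservative. The sentence naming the test directly follows associations between ratings and app log data, which arise in the app arm. The article describes no between-arm rank test, so the argument applies only if the test is also used that way.

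Finally, the SD inflation rests on an assumed d, errs towards a larger future trial and is within sampling noise. The unadjusted SD is the right input if that trial does not adjust for sex. All of this stands, and it limits the size of the point. It does not explain why a factor important enough to double the sample is absent from the stated analyses.

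A separate weakness lies in the quoted phrase. A parallel-group trial has no paired differences, and no outcome is named for the SD, so saying that it is within sex would not by itself define it.

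**Conclusion.** The concern holds in a limited form. Sex is the stratification factor and the only stated reason for 40 participants in place of 20, and neither the stated analyses nor the planning SD uses it. The consequence is an SD that may be too large by about 3% (d = 0.5) to 12% (d = 1), with a future sample size 6% to 25% too large.

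These figures assume an equal sex split, a common within-sex SD, a sex difference that the article does not give, and a future trial that stratifies or adjusts for sex. Within this range the error is conservative and smaller than the uncertainty of any SD from 40 people. It is a free improvement and does not threaten the pilot's conclusions.

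**What to change.** - **Power calculations:** name the 1-month outcome. Define the planning quantity as the SD (or, for a binary outcome, the proportion variance) computed within arm and sex and then pooled. Report the unadjusted value beside it, with intervals, so that the future trial can use whichever matches its analysis.
- **Data analysis:** tabulate recruitment, retention, app engagement and 1-month smoking status by sex with confidence intervals, labelled descriptive because there are only 10 per sex per arm. Because enrolment is fixed by sex, show recruitment as consent among eligible patients approached.
- **Rank test:** if one is used to compare arms, stratify it by sex (van Elteren). The associations between ratings and app log data within the app arm need no change.

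The cost is analysis wording only. Sex is already recorded for the stratification, and neither the sample size, the data collection nor the conduct of the trial changes.

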## Discussion

This pilot trial will be the first to evaluate a commercially available smartphone app for tobacco cessation in a hospitalized setting. The study offers a research/industry collaboration that allows the study to leverage resources from two directions: (1) providing cutting-edge research tools and methods founded on evidence-based academic research and (2) applying translational and implementation strategies from the software development team.

We have chosen a pragmatic approach in order to simulate more real-world settings in app usage. Indeed, the effectiveness of off-the-shelf tobacco cessation apps is compromised by the rapid development cycle of mobile apps and urgency for apps to be quickly released and profitable. Data generated by this study can be used for larger fully powered trials such as comparative effectiveness studies against apps developed by health scientists based on behavioral theories or cost-effectiveness analyses of mobile interventions.

## Trial status

Protocol version: 4

Trial registration: ClinicalTrials.gov

Registration number: NCT03538678 (https://clinicaltrials.gov/ct2/show/NCT03538678)

Date of trial registration: 28 May 2018

Was this trial prospectively registered? Yes

Date recruitment began: June 2018. Recruiting is ongoing

Anticipated completion date: May 2019.

## Abbreviations

FITT: Fit between individuals, task and technology
IRB: Institutional review board
mHealth: Mobile health
NCI: National Cancer Institute
PI: Principal investigator
RCT: Randomized control trial
REDCap: Research Electronic Data Capture
TTS: Tobacco Treatment Service
